### Safety, reporting of adverse events and serious adverse events

The main adverse events anticipated in this study are skin rashes from the accelerometer, and falls, cardiac ischaemia or pulmonary embolism during exercise. All adverse events are recorded using an adverse event recording worksheet, and causality to the study intervention is determined, in consultation with the treating physician, by a study physician ([name]). The Sponsor’s Clinical Research Supporting Officer is notified electronically, within 24 h, of any serious adverse event that occurs during the trial. From a previous local longitudinal study, the Cork Dementia Study, the in-hospital mortality of this cohort is expected to be approximately two per cent [18]. This predicts approximately 5 deaths of trial subjects. However, the type of exercise involved is similar to usual care, patients with a contraindication to exercise will be excluded at source, and patients who are unwell on a particular day will not exercise.

### Statistical analysis

The results will be analysed and presented as recommended by the CONSORT guidelines [30]. The primary outcome measure will be length of stay. This will be described using Kaplan-Meier “survival” curves and the results between groups will be compared using a log-rank test. Univariate and multivariate linear regression analysis will be used to determine differences in physical activity in hospital and physical performance, quality of life at discharge and three months post-discharge, and re-admission rates at three months.

This analysis will help to define whether a simple physiotherapy-led exercise intervention will shorten length of stay, increase physical activity in hospital, limit functional decline and readmission rates and improve quality of life in frail older hospitalised patients.

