### Physical activity levels and exercise intervention for medical patients in hospital

Recent evidence has shown that older medical patients walk an average of 1534 (±112) steps per day in hospital and that prolonged length of stay was inversely associated with daily step count, even when adjusted for age, gender and physical performance on admission [7]. Similarly, Fisher et al. [8] found that older adults, who increase their walking activity by 600 steps on the second day of observation, were discharged home two days earlier. These findings suggest that low physical activity in hospital may directly influence length of stay and supports the theory that patients should exercise and remain active in the acute setting. Exercise programmes in hospital have been delivered independently or as a component of a multidisciplinary intervention and have been shown to improve physical performance, quality of life, reduce falls incidence and reduce healthcare utilisation [9–13].

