## Methods

### Design and study size

The study is a single blind randomised controlled trial set in an acute 350-bedded teaching hospital. Power calculations based on the results of a pilot study indicated that a sample size of 200 (100 patients in each arm) would be required. To allow for an expected attrition rate of 5 % [18], two hundred and twenty medical patients aged 65 years and over are randomly allocated to either the intervention or sham arm in a ratio of 1:1. (see Fig. 1). The study has been approved by the Clinical Research Ethics Committee of the Cork Teaching Hospitals. (ECM 3 (vv) 13/10/15).

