### Measurements

Patients are assessed within 48 h of admission, at discharge and at three months following discharge. The assessment tools are described in Table 1. Baseline data includes demographics, co-morbidity, medication use and home circumstances.

**Table 1 Tab1:** Summary of the Measurements used in the Study

Domain	On admission	Discharge and 3 months
Medical Morbidity	Cumulative Illness Rating Scale (CIRS-G [19]);	
	Total number of medications	
Frailty	SHARE- FI [20]	Grip Strength (kgs)
Physical Performance	Short Physical Performance Battery (SPPB) (includes walking speed) [22]	SPPB [22] (includes walking speed)
Falls Efficacy and Self-Reported Functional Ability	Number of Falls and injuries sustained	Number of falls and injuries sustained
	Falls Efficacy Scale – International (FES-I) [25]	Nottingham Extended Activities of Daily Living Scale (N-EADL) [26]
	Nottingham Extended Activities of Daily Living Scale (N-EADL) [26]	
Cognition	6CIT [21]	6CIT [21]
Quality of Life	EQ-5D-5 L [24]	EQ-5D-5 L [24]
Physical Activity	Accelerometers (Stepwatch Activity Monitor, SAM) during hospitalisation only	

The primary outcome measure is length of stay, a key healthcare utilisation metric. The secondary outcome measures includes patient-related measures: changes in physical performance (SPPB, walking speed), and quality of life at 3 months following discharge, differences in physical activity levels between groups in hospital (based on accelerometry data) and re-admission rates over three months. The baseline assessment is designed to capture frailty, co-morbidity and disability. Measurements that are appropriate and quick to administer have been chosen to limit patient fatigue.

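### The primary length-of-stay comparison is an unadjusted log-rank test that leaves baseline covariates unused: valid, but inefficient by an amount the documents cannot fix

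*Protocol article*

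**What the plan says.** The Statistical analysis section states: "The primary outcome measure will be length of stay". It continues: "This will be described using Kaplan-Meier “survival” curves", and "the results between groups will be compared using a log-rank test". No covariate or stratification factor is attached to that test. The next sentence sets out regression for other outcomes: "Univariate and multivariate linear regression analysis will be used to determine differences in physical activity in hospital and physical performance, quality of life at discharge". It goes on to the three-month assessments and re-admission. Length of stay is not in the list. The section opens with a general commitment: "The results will be analysed and presented as recommended by the CONSORT guidelines".

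Under Measurements, "The baseline assessment is designed to capture frailty, co-morbidity and disability". Table 1 places CIRS-G, SHARE-FI, SPPB and 6CIT in the admission column, and the text adds demographics. The section on consent, assessment and exercise procedure puts this assessment (Time 1) before allocation. The section on selection and allocation describes blocks of about 50 and states no prognostic stratification.

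On sample size, pilot-based power calculations "indicated that a sample size of 200 (100 patients in each arm) would be required", which the protocol raises to 220.

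**The concern.** The trial gathers frailty, co-morbidity and physical performance on every patient before allocation. As stated, neither the randomisation nor the primary test uses them. Regression with several covariates is planned for the secondary outcomes only.

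If those measures predict how long a patient stays, an unadjusted comparison leaves that variation in the noise. At stake is power for the primary outcome in a trial planned around 200 patients, in a field where, by the protocol's own account, three earlier trials of additional exercise alone found no significant improvement in stay. The protocol states this choice of test, so it can be assessed as a choice and not merely as a detail left out.

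**Working it through.** **Inputs from the protocol.** 200 patients required and 220 randomised, 1:1; in-hospital mortality about 2%; log-rank test as above.

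**Inputs assumed.** Two-sided alpha 0.05, base power 80%, and the share R² of the variance of log stay explained by the covariates. The protocol gives none of these.

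**1. The plan's figure of 200.** It cannot be reproduced, because alpha, power and effect size are not stated in the article. It can be back-solved with the Schoenfeld formula at 1:1 allocation:

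HR = exp[(z for alpha + z for power) / √(events/4)]

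Events = 0.98 × 200 = 196, so √(196/4) = 7.
- 80% power: exp[(1.960 + 0.842)/7] = 1.49.
- 90% power: exp[(1.960 + 1.282)/7] = 1.59.

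So 200 is consistent with a discharge hazard ratio near 1.5, but this is an inference.

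**2. Gain from a fixed unadjusted power (ANCOVA on log stay).** Adjustment multiplies the residual variance by (1 − R²):

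adjusted power = Φ[(1.960 + 0.842)/√(1 − R²) − 1.960]; equivalent unadjusted N = 200/(1 − R²)

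| R² | Adjusted power | Equivalent N |
|---|---|---|
| 0 | 80% | 200 |
| 0.05 | 82% | 211 |
| 0.10 | 84% | 222 |
| 0.20 | 88% | 250 |
| 0.30 | 92% | 286 |

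From an assumed base of 90%, the same formula gives 91%, 93%, 95% and 97% for R² of 0.05 to 0.30.

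**3. Gain with the conditional hazard ratio held fixed (simulation).** Exponential stays, n = 200, 2% censored, one composite covariate with coefficient g, conditional hazard ratio 1.5, 3,000 replicates. On the log-time scale R² = g²/(g² + π²/6).

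| R² | Log-rank power | Adjusted Cox power |
|---|---|---|
| 0 | 82% | 81% |
| 0.04 | 77% | 81% |
| 0.13 | 66% | 80% |
| 0.25 | 54% | 80% |

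The Monte Carlo standard error is at most √(0.5 × 0.5/3,000) = 0.9 points. With no treatment effect, both methods rejected in 4.3% to 5.6% of replicates, so both hold the nominal 5%.

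A second simulation (n = 220, conditional hazard ratio 1.45, 1,500 replicates) shows the same pattern: 64% against 76% at R² 0.10, where the unadjusted hazard ratio shrinks to 1.39.

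**4. Why steps 2 and 3 differ.** Step 2 fixes the unadjusted power and lets adjustment reduce the variance. Step 3 fixes the effect within covariate levels, so the unadjusted hazard ratio moves towards 1 as R² rises. The article does not say which kind of effect the pilot-based calculation used. Step 2 is the more cautious statement of the gain.

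**The case against.** The strongest reply is that nothing here is wrong. A log-rank test is valid after randomisation, needs no choice of covariates or functional form, and cannot lose patients to missing covariates. The adjusted Cox hazard ratio is also a conditional effect, which is a different quantity from the unadjusted one. All of this stands, and it is why the point concerns efficiency only.

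The documents also do not show that the covariates predict stay. The Background cites a study in which "prolonged length of stay was inversely associated with daily step count, even when adjusted for age, gender and physical performance on admission". That shows which adjusters were used, not how strong they were. CIRS-G is described as a predictor of 18-month mortality and hospitalisation, which is not length of stay. Eligibility narrows the range of function: patients need an aid or assistance, are not bed- or chair-bound, and those with SPPB below 1 are eliminated. This stands too, so no single figure for the loss can be defended.

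Two stronger readings are tempting, and the documents support neither.
- A reader might take a gain such as the 14 points (66% to 80%) or 26 points (54% to 80%) in step 3 as the trial's actual loss. Those figures depend on the assumed R² and on a fixed conditional hazard ratio.
- A reader might infer that the plan yields no effect estimate. The article names none beside the test, but Kaplan-Meier curves allow medians by arm to be read, the CONSORT commitment points towards reporting an effect, and an analysis plan that is not shown may name the measure. The section asks whether stay is shortened, and a log-rank test can answer that.

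What the objection does not remove is that the article assigns an unadjusted test to the primary outcome and lists regression for the others.

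**Conclusion.** The point holds as a weakness in efficiency. The primary comparison as stated uses none of the prognostic candidates measured before allocation, and no stratified randomisation is stated that would use them instead. Type I error is not affected.

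The size is unknown. From an assumed 80% base the gain is about 2 to 12 points for R² of 0.05 to 0.30 under log-scale ANCOVA. It is larger if the conditional hazard ratio is held fixed, and about zero if the covariates do not predict stay. These results rest on assumed alpha, base power and R²; step 3 also assumes proportional hazards, exponential stays and a correctly specified covariate. In the simulation, adjusting for a covariate with no predictive value cost about one point or less. The change is therefore worth making even though its benefit cannot be promised.

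**What to change.** Before unblinding, state one primary analysis: a Cox model for time to live discharge, with arm plus a short pre-specified set of baseline covariates, for example SPPB, CIRS-G, SHARE-FI and age. Report the hazard ratio with its 95% confidence interval. Keep the unadjusted log-rank test and the Kaplan-Meier curves as supportive. Name a single model, because offering alternatives such as Cox or Fine-Gray would leave the estimand open.

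The cost is analysis wording; the example covariates are already collected, and no visits or patients are added. The covariates, their functional form and the handling of missing values must be fixed in advance, and the report should say that the adjusted hazard ratio is a conditional effect.

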Patient compliance, exercise prescription and session duration is recorded. Within one day of planned discharge, all patients are re-assessed and the accelerometer (SAM) is removed from the patient by the RPT (Time 2; see Table 1). Patients who are deemed for long-term care (as they are unable to manage at home) or for end-of-life care are re-assessed on the date that the decision is made and those results are used.

The patients are reassessed at three months post discharge, by the RPT (Time 3, see Table 1). New onset of illness, physical performance, walking speed, quality of life and self-reported functional ability is measured. Hospital and Accident and Emergency utilisation since discharge is recorded.

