Up to 27 % of the patients were unable to complete the Timed Up and Go Test in previous studies [16,17]. Therefore, the Short Physical Performance Battery will be used, which was found to be feasible and sensitive to change in a previous pilot study [13]. Length of stay will be used as the primary outcome measure as this is available electronically and absolutely complete data. A high attrition rate is predicted for the three-month follow-up attendance as our study group consist of frailer older adults.

A small number of studies have shown that interventions to increase older medical inpatients’ physical activity can be modestly beneficial. Previous authors discuss issues such as patient selection, intervention type and outcome measures. This protocol has been designed to include the frailer patient, to include a tailored and comprehensive intervention, and to measure the effects with the most valid outcome measure.

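### Re-admission at three months, a yes/no or small-count outcome, is assigned to linear regression; a binary or count model should be named instead

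*Protocol article*

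**What the plan says.** The Measurements section makes "re-admission rates over three months" a secondary outcome. It does not say whether this means the proportion of patients re-admitted at least once or the number of re-admissions per patient.

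The Statistical analysis section describes length of stay by Kaplan-Meier curves and compares it by a log-rank test. For everything else it gives one sentence: "Univariate and multivariate linear regression analysis will be used to determine differences in physical activity in hospital and physical performance", which continues with "quality of life at discharge and three months post-discharge, and re-admission rates at three months". Re-admission is therefore explicitly under the linear model. No logistic, Poisson, negative binomial or time-to-event method is named for it anywhere in the article.

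The section on consent, assessment and exercise procedure states what is collected: "Hospital and Accident and Emergency utilisation since discharge is recorded". It sets one nominal window for all patients: "The patients are reassessed at three months post discharge, by the RPT".

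Two statements bear on how complete that window will be. The safety section says "the in-hospital mortality of this cohort is expected to be approximately two per cent", and the Discussion says "A high attrition rate is predicted for the three-month follow-up attendance as our study group consist of frailer older adults".

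**The concern.** SPPB, walking speed, EQ-5D and step counts can reasonably go into a linear model. Re-admission is different in kind. Per patient it is 0 or 1, or a count that will mostly be 0, 1 or 2. Its variance depends on its mean, it cannot fall below zero, and as a yes/no variable it cannot exceed one. A linear model with covariates respects none of these limits.

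A rate in the strict sense also needs time at risk in its denominator, and the named model has none. A patient who dies or is lost soon after discharge without a re-admission has the same value as one observed free of re-admission for the full three months.

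What is at stake is how one secondary outcome is estimated and reported. The primary outcome has its own method and is not affected. Because the method is stated, this is not a detail left to an analysis plan that is not shown.

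**Working it through.** The documents give no re-admission rate and no figure that depends on this model, so there is nothing to reproduce. Every rate below is an assumption unless a section is named.

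**Inputs from the protocol article.** 220 patients randomised 1:1 (Design and study size); three-month window (Consent, assessment and exercise procedure); in-hospital mortality about 2%, that is 0.02 × 220 = 4.4 patients, which agrees with the roughly 5 deaths predicted in the safety section; high attrition at the three-month visit, with no figure (Discussion).

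**Step 1. Unadjusted contrast, equal follow-up.** Linear regression of outcome Y on arm returns the difference in means, mean(Y₁) − mean(Y₀). For a 0/1 outcome this is the risk difference. With 105 per arm (close to 220 × 0.95 = 209 in total), 20,000 simulated trials per setting and no true effect, the two-sided 5% test rejects as follows:

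- yes/no outcome, risks of 10%, 20%, 30% and 40%: 5.0%, 4.8%, 4.9% and 5.0%
- counts: 4.6% (mean 0.3, Poisson), 4.7% (mean 0.3, overdispersed) and 4.9% (mean 0.5, overdispersed)

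The unadjusted comparison holds its level.

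**Step 2. Multivariate model, equal follow-up.** Take n = 200, 1:1, no true arm effect and three standard-normal covariates, with logit(risk) = log[p/(1 − p)] + 0.8x₁ + 0.5x₂ + 0.5x₃. Fit ordinary least squares of the 0/1 outcome on arm and covariates, with ordinary standard errors (10,000 runs per setting).

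| p (risk at average covariates) | Overall risk | Fitted risks outside 0 to 1 | Type I error, arm | True SD of arm estimate | Mean reported SE |
|---|---|---|---|---|---|
| 15% | 19% | 9.8% | 5.0% | 0.052 | 0.052 |
| 25% | 29% | 6.4% | 4.8% | 0.060 | 0.059 |
| 30% | 33% | 5.2% | 5.1% | 0.061 | 0.061 |

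If the overall risk is instead held at 15%, 25% and 30%, the out-of-range shares are 11.6%, 7.7% and 6.1%. Almost all the impossible values lie below zero. The test and the standard error for the arm effect are not disturbed.

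**Step 3. Unequal time at risk, counts.** Assume the same true rate in both arms, 0.4 re-admissions per patient per three months. A fraction q of patients leaves observation at a uniformly distributed time, so they contribute half the window on average. The expected count is then 0.4 × (1 − q/2). For q = 10% it is 0.4 × 0.95 = 0.38; for q = 30% it is 0.4 × 0.85 = 0.34; the ratio is 0.34/0.38 = 0.895 although the true rate ratio is 1. Results for 105 per arm, 20,000 runs:

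| Early exit by arm | Expected counts | Ratio of means | Linear model rejects | Rate model with offset rejects |
|---|---|---|---|---|
| 10% vs 10% | 0.38, 0.38 | 1.000 | 4.9% | 4.7% |
| 10% vs 20% | 0.38, 0.36 | 0.947 | 5.6% | 4.8% |
| 10% vs 30% | 0.38, 0.34 | 0.895 | 7.3% | 4.6% |
| 5% vs 25% | 0.39, 0.35 | 0.897 | 7.5% | 4.9% |

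The rate model with a person-time offset estimates a rate ratio of 1.00 in every row.

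**Step 4. Unequal deaths, yes/no outcome.** Take a full-window risk of 25% and deaths of 5% versus 10%. A patient who dies loses about half the window and so about half the risk. The bias is about 0.25 × ½ × (0.10 − 0.05) = 0.006, or 0.6 percentage points. The standard error with 105 per arm is about 5.9 points, and the simulated type I error is 5.1%.

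**The case against.** The strongest reply is that the trial asks about the difference between arms, and linear regression answers that acceptably. Steps 1 and 2 bear this out. A reader might infer from the wrong model that the standard errors for the treatment effect are wrong; the calculations do not support that. Impossible fitted risks matter for individual prediction, which the article does not plan. This stands, and it limits the point.

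A reader might also infer that the analysis will favour whichever arm has more deaths. The documents do not support that as a prediction. They set the same window for everyone, give no mortality after discharge, and offer no reason to expect deaths to differ by arm. The predicted attrition concerns attendance at the three-month visit. Consent covers access to medical notes, so a missed visit need not mean a lost re-admission record. The bias is conditional, and at 5% versus 10% deaths it is negligible.

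A reader might further treat re-admission as the safeguard against a shorter stay bought with early returns. That is a sensible clinical thought, but the article gives the outcome no such role.

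Finally, competing-event methods, composites and the choice of effect measure can be left to an analysis plan, and their absence from a journal article is no fault. What the reply does not remove is that the article names a model, and the model does not match the outcome.

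**Conclusion.** The point holds in a limited form. The Statistical analysis section assigns linear regression to an outcome that per patient is binary or a small count, and names no alternative.

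Under the assumed covariate effects, about 5% to 10% of fitted risks from the multivariate model are impossible (up to 11.6% if the overall risk is 15%). The treatment contrast keeps about 5% type I error when follow-up is equal. Ignoring time at risk does material harm only if early exit differs clearly by arm: roughly 10% versus 30% is needed to take the false-positive rate to about 7%. That gap is an assumption; the documents give only about 2% in-hospital mortality and an unquantified expectation of high attrition.

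One secondary outcome is affected and the primary is not, so this is minor to should-fix. Calling it an essential correction would go beyond what the documents and the calculations show.

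**What to change.** In the Statistical analysis section, remove re-admission from the linear-regression sentence. State which quantity is meant and name the matching model:

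- for any re-admission within three months of discharge, logistic regression, or modified Poisson regression with robust standard errors; or
- for the number of re-admissions, negative binomial regression with log days alive and observed since discharge as offset. Patients who die in hospital have no time at risk and do not enter this model.

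Keep linear regression for SPPB, walking speed and EQ-5D.

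The cost is analysis wording. The utilisation data are already to be recorded at three months. If the offset is used, confirm that dates of death and of last observation are captured.
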